### Participant Compliance

During the treatment period participant's compliance will be assessed. Participants will be asked directly whether they have been wearing their bandage. Any episodes of non-compliance will be documented and the circumstances and duration recorded in the CRF. Should there be questions or consideration of deviation from the Protocol, clarification will be sought from the Study Coordinator. Any study participant treated in a manner that deviates from the Protocol, or who is admitted into the study but is not qualified according to the Protocol, may be ineligible for analysis.

### Randomisation

Randomisation will follow a computer generated allocation schedule (NQuery version 7), using allocation concealment to prevent prior knowledge of treatment assignment. Numbers will be assigned in strict chronological sequence and study participants will be entered in sequence. Randomisation in small block sizes (2 and 4) will be stratified by wound clinic site and wound size ≤ 10 cm^2 ^or >10 cm^2 ^(assessed from the wound tracings and digital photography). Each study participant will be allocated a unique randomisation number on successful completion of screening.

Patients will be randomised to receive either control or intervention group using a central computer generated random number generated by using a central computer generated randomisation sequence. The randomization code will be sent to the Investigator (or designee) who will prepare treatments according to the randomisation code.

To decrease bias and confounders the decision to accept or reject a participant will be made using inclusion and exclusion criteria. Informed consent will be obtained from participants prior to obtaining the randomisation code. Independent clinicians will assess the eligibility of the patient, input identifiers on the randomisation website interface to document eligibility and obtain the randomisation number and allocation of bandage type. The compression bandage systems will be applied according to the computer generated list allocation. The codes will only be revealed to the researchers once the recruitment, data collection and wound measurement analysis are completed. The allocation list will be stored within the Clinical Informatics and Data Management Centre of the DEPM.

### Plan and Trial Design

This pilot study is a randomised, multi-centre clinical trial to evaluate the efficacy and safety of graduated three layer straight tubular bandaging (intervention arm) compared with standard compression therapy (control arm) in participants with chronic venous ulceration. Neither participants nor study staff will be blinded to treatment. Screening evaluations will ensure that potential participants fulfil all requirements for entry into the study. Forty six study participants will be randomised (1:1) to either intervention arm or to the control arm of the study. Study participants will be reviewed weekly during the 12 week treatment period, and if healed in treatment period, participant will be also be reviewed monthly for three months during a subsequent follow up period.

In the following sections, a detailed description of all study procedures is given. All study visits and procedures are described and the evaluations performed at each visit are detailed. An overview and schedule of the visits and procedures is provided in Table 1.

**Table 1 T1:** Study Schedule

		Screening Period		Treatment Period Weeks													Follow-Up Period Months		
	
		Screening visit		Day 1	1	2	3	4	5	6	7	8	9	10	11	12	Month1	Month2	Month3
Informed Consent		X																	

Inclusion Criteria		X																	

Exclusion Criteria		X																	

Randomisation		X																	

Medical history		X																	

Physical Examination		X														X	X	X	X

Vital Signs		X		X	X	X	X	X	X	X	X	X	X	X	X	X	X	X	X

Intercurrent Illness		X		X	X	X	X	X	X	X	X	X	X	X	X	X	X	X	X

Intercurrent Medication		X		X	X	X	X	X	X	X	X	X	X	X	X	X	X	X	X

Tolerability Assessment				X	X	X	X	X	X	X	X	X	X	X	X	X	X	X	X

Target ulcer assessment		X		X	X	X	X	X	X	X	X	X	X	X	X	X	X	X	X

SF 36 and CWIS				X												X			X

Adverse events				X	X	X	X	X	X	X	X	X	X	X	X	X	X	X	X

Compression hosiery fitting/ application		X														X^2^			

Check for Ulcer Recurrence																	X	X	X

Care of ulcer information sheet		X														X^2^	X^4^	X^4^	X^4^

Referred back to specialty wound clinic																X^3^	X^4^	X^4^	X^4^

X^2^: If healed.

X^3^: If not healed.

X^4^: If ulcer has recurred.

*: If target ulcer has completely healed, (defined as 100% epithelialisation with no presence of exudate or scab).

### Screening Evaluation

The screening period will last for one week during which time study participants will be required to wear compression bandages as randomised. Prospective participants will be informed about all aspects of the clinical study, including procedures, risks and benefits. Receipt of this information will be acknowledged for each study participant through the provision of written informed consent by the participant. A copy of the information sheet and consent form will be provided to each participant.

The following screening assessments will be conducted for each potential participant:

Informed consent; assessment of compliance with the inclusion and exclusion criteria; patient medical history; concomitant medications and treatments; physical examination and target ulcer assessment.

### Treatment Period - Day 1

Participants will be bandaged according to their random number allocation. The intact standard compression bandage should be removed and the target ulcer and limb thoroughly cleansed with tap water and soap-free wash. The wound may be debrided if deemed clinically necessary as sloughy and exudative wounds with unhealthy wound beds will take longer to heal. Wound debridement and exudate management is important in early stages to ensure adequate wound bed preparation.

The following assessments will be conducted for each participant: Target Ulcer Assessment, Temperature, pulse and blood pressure, intercurrent illness and medication, SF 36 and CWIS Quality of Life, Adverse Events and confirmation of next visit (7 days time).

### Treatment Period - Weeks 1 to 12

Participants will return to the study centre weekly following Day 1 for the following assessments: Check whether the wound has healed, Target Ulcer Assessment, Assessment of tolerability of product (very comfortable, comfortable, uncomfortable, very uncomfortable), Temperature, pulse and blood pressure, intercurrent illness and medication, Adverse Events, SF 36 and CWIS Quality of Life (Week 12 only)

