##### Exclusion Criteria

Study participants who meet any of the following criteria will not be eligible for participation in this study:

1. Unable or unwilling to wear compression bandage as directed

2. Evidence of severe liver disease, cardiac disease or chronic pulmonary disease

3. Medical condition likely to require systemic corticosteroids during the study period

4. Any significant condition that may preclude the participant from the study (e.g. severe depression or psychiatric illness)

5. Clinically suspected deep vein thrombosis

6. Unable or unwilling to attend clinic for routine treatment

7. Participation in this trial previously and/or who dropped out or were withdrawn

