### Duration of Treatment Including Follow-Up

The ulcer will be dressed weekly with standard compression bandage for one week run in period. The treatment period is 12 weeks duration. All participants will be seen on a weekly basis by an experienced leg ulcer practitioner. Additional visits may be necessary if clinically indicated. Study participants randomised to the intervention group will be treated with graduated three layer straight tubular bandage system once per week for 12 weeks. Study participants randomised to the control group will be treated with standard compression bandage for 12 weeks.

Study participants whose ulcers heal before or at 12 weeks of treatment will be assessed monthly for 3 consecutive months during the Follow-Up Period to monitor for safety and target ulcer recurrence rates. Study participants whose ulcers have not healed at the 12 week visit will be released from the study and returned to the care of the speciality wound clinic. All care will be made to ensure that all adverse events are followed until resolution.

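### Compression is worn during the screening week, but scheduled adverse-event, tolerability and compliance recording starts only afterwards, so early intolerance can be under-counted

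*Protocol article*

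**What the plan says.** All places are in the protocol article.

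- **Exposure.** Screening Evaluation: "The screening period will last for one week during which time study participants will be required to wear compression bandages as randomised". Duration of Treatment Including Follow-Up describes the same week differently: "The ulcer will be dressed weekly with standard compression bandage for one week run in period". The Day 1 text fits the second description: "The intact standard compression bandage should be removed".
- **Time of randomisation.** Table 1 marks it at the screening visit. The Randomisation section says "Each study participant will be allocated a unique randomisation number on successful completion of screening".
- **Screening assessments.** The list reads "Informed consent; assessment of compliance with the inclusion and exclusion criteria; patient medical history; concomitant medications and treatments; physical examination and target ulcer assessment". It has no adverse-event, tolerability or bandage-compliance item.
- **Start of recording.** In Table 1 the row "Tolerability Assessment" and the adverse-event row are empty at screening and begin at Day 1. The Day 1 text includes adverse events but not tolerability, which the text first lists for Weeks 1 to 12. On compliance: "During the treatment period participant's compliance will be assessed".
- **Withdrawal.** Criteria for Participant Withdrawal allows withdrawal at any time, including for not wearing the bandage. It asks for adverse events to be documented and, where possible, the reasons for leaving. It names no start date.
- **Eligibility.** Exclusion 1 is "Unable or unwilling to wear compression bandage as directed".
- **Outcomes that use these data.** Secondary outcomes 2 (treatment-related adverse events), 3 (acceptability, measured by withdrawals), 4 (adverse effects and serious adverse events) and 6 (self-reported compliance).

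**The concern.** The first week in a compression bandage is a natural time for discomfort or refusal to show, and here it falls before the scheduled recording of those things. The patients who tell us most about acceptability are those who stop, and they are the ones who may not attend Day 1. Better tolerance and adherence are part of the stated case for the three-layer system (Background; Rationale for Conducting the Trial), so an incomplete count bears on a question the pilot is meant to inform. Staff are not blinded. An unclear line between screen failure and withdrawal therefore leaves room for the classification to depend on the bandage worn.

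**Working it through.** **1. Is there exposure without scheduled recording?** The adverse-event row of Table 1 has 16 marks: Day 1, 12 weekly visits and 3 monthly visits (1 + 12 + 3 = 16). None is at screening. Vital signs, intercurrent illness and intercurrent medication do carry a screening mark, so the table separates rows that start at screening from rows that do not. Bandages are worn for 1 + 12 = 13 weeks, and the screening week is the first of them.

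**2. What can still be recovered?** Day 1 closes that week.

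| Item | Patient returns at Day 1 | Patient stops before Day 1 |
|---|---|---|
| Adverse events | Day 1 entry can look back | No scheduled entry; general withdrawal rule only |
| Tolerability | Marked in Table 1, absent from the Day 1 text | No scheduled entry |
| Compliance | Not collected for that week | Not collected |
| Withdrawal | Not applicable | Counts if labelled a withdrawal; not if labelled a screen failure |

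**3. How does the answer depend on what happens in that week?** The text allows three readings.

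- *Randomised at screening, allocated bandage worn* (Screening Evaluation, Table 1). A failure occurs after allocation and should be a withdrawal. Exclusion 1, and the rule that the number follows successful screening, permit a screen-failure label instead.
- *Standard bandage first, then randomisation* (Duration of Treatment, Randomisation). A failure is never randomised. Acceptability is then compared only among people who completed a week in the standard bandage.
- *Randomised at screening, standard bandage until Day 1* (Table 1 with the Day 1 text). A failure on the standard bandage belongs to whichever arm was allocated, including three-layer.

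**4. Size.** The denominator comes from Sample Size and Analysis plan. With a difference of 0.47, SD 0.5, two-sided alpha 0.05 and 80% power, n = 2 × (1.96 + 0.84)² × 0.5² / 0.47² ≈ 17.7, rounded up to 18 per group. Allowing 20% loss, 18 / 0.8 = 22.5, so 23 per arm and 46 in total. The plan's figures reproduce.

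Where allocation precedes the week, one uncounted failure lowers that arm's rate by 1/23 = 4.3 percentage points, and two by 2/23 = 8.7. If the person also leaves the denominator, k/23 becomes (k − 1)/22, a drop of (23 − k)/506: 4.3 points at k = 1 and 18/506 = 3.6 at k = 5.

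The documents give no first-week failure rate. Assumed rates of 5%, 10% and 20% would mean 23 × 0.05 = 1.2, 23 × 0.10 = 2.3 and 23 × 0.20 = 4.6 people per arm. This range is illustrative. How many of them would go uncounted depends on how sites label them.

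**The case against.** Four points have weight.

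- **Loss is not certain.** A reader might infer that everyone who fails in the first week is missing from the safety and acceptability outcomes. The documents do not support that. The withdrawal section has no Day 1 start, and outcome 3 is measured by withdrawals, so a randomised patient who stops in week one ought to be counted. This stands. What the section does not settle is whether such a person is a withdrawal or a screen failure.
- **The week is not wholly unrecorded.** A reader might also infer that one of 13 weeks lies outside the recording window. For those who return, Day 1 can capture its events, so that is too strong. It does not help with compliance or with those who do not return.
- **The 4.3 points are conditional.** They have no meaning for a run-in before randomisation. Setting them against the plan's 20% loss would also mislead, because that allowance concerns missing 12-week wound areas. Likewise, a reader might conclude that a standard-bandage run-in favours short stretch. The direction is plausible, but no failure rates are given to show it, and selecting people able to wear compression is already an eligibility choice.
- **This is a condensed article.** Form wording and separate monitoring guidelines are not shown. But Plan and Trial Design says it sets out every visit and what is assessed at each, and the start points are stated. The objection therefore covers details left unwritten, not a stated window that omits exposure.

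The underlying fault is the contradiction over that week. Resolving it removes some readings, but under each one the start of recording and the status of early stoppers still need stating.

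**Conclusion.** The concern holds in a limited form. Compression starts before scheduled adverse-event, tolerability and compliance recording does. First-week compliance is not collected, a patient who stops before Day 1 has no scheduled record, and the wording allows that patient to be treated as a screen failure. Early intolerance can therefore be under-counted in secondary outcomes 2, 3, 4 and 6; it is not shown that it will be. The size is 4.3 percentage points of an arm's rate per randomised patient lost, assuming 23 per arm and allocation before the week. The number of such patients is unknown. The primary outcome is not at issue here. This is a cheap improvement.

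**What to change.** 1. Reconcile Randomisation, Table 1, Screening Evaluation, the Day 1 text and Duration of Treatment on when randomisation occurs and which bandage is worn in the screening week. This point does not depend on which is chosen.
2. Start adverse-event, compliance and withdrawal recording at the first study bandage application, and reword Participant Compliance to match. Have Day 1 look back explicitly over the week for events, tolerability and compliance, and bring the Day 1 text into line with Table 1 on tolerability. A mark in the screening-visit column alone would add little, because wear only begins there.
3. Count everyone randomised in the denominators of outcomes 2, 3, 4 and 6, including those who stop before Day 1, and class them as withdrawals.
4. If the week is a standard-bandage run-in before randomisation, log those who stop, report them by reason, and state that the acceptability comparison applies to people who completed that week.

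The cost is minor case report form wording and, under item 4, a short log and a slightly narrower acceptability claim. No visits or staff are added. The article reports 25 of 46 recruited, so the change could still apply to the remaining 46 − 25 = 21.

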### Summarized Details of Investigational Products

The Investigational Product being studied is *Tubular - Form*; an elastic tubular bandage. Tubular form is listed with TGA (AUST L 59144) as a treatment for varicose conditions and control of oedema. In this study the investigational product will be used in graduated lengths of 3 layers of the tubular bandage system as follows:

1. from base of toes to just under knee (long layer)

2. from base of toes to above calf pump (medium layer)

3. from base of toes to mid gaiter (short layer)

The control group will be treated with standard short stretch compression therapy which consists of:

1. a padding layer

2. inelastic short stretch compression bandage

3. a tubular stocking

All layers of standard compression therapy will be applied from base of toes to just under the knee.

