#### Primary Outcome

The percentage reduction of wound area from baseline compared to week 12 following randomisation. The size of the wound area will be measured by Visitrak wound measurement system and wound digital photographs.

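### The protocol gives two incompatible accounts of the bandage worn in the screening week, so the primary endpoint's baseline area may be measured after a week of allocated treatment

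*Protocol article*

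**What the plan says.** **Bandage in the week before Day 1.** Screening Evaluation: "The screening period will last for one week during which time study participants will be required to wear compression bandages as randomised". Duration of Treatment Including Follow-Up: "The ulcer will be dressed weekly with standard compression bandage for one week run in period". The Day 1 text agrees with the second account: "The intact standard compression bandage should be removed and the target ulcer and limb thoroughly cleansed with tap water and soap-free wash". It also says: "Participants will be bandaged according to their random number allocation". Standard compression is the comparator, as the section on investigational products shows: "The control group will be treated with standard short stretch compression therapy which consists of" a padding layer, an inelastic short stretch bandage and a tubular stocking.

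**Time of randomisation.** Table 1 has its only randomisation mark in the screening-visit column. The Randomisation section says: "Each study participant will be allocated a unique randomisation number on successful completion of screening".

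**Endpoint.** The primary outcome is: "The percentage reduction of wound area from baseline compared to week 12 following randomisation". The sample size section analyses log(Area2/Area1), with Area1 the baseline area. Table 1 schedules a target ulcer assessment at both the screening visit and Day 1. The treatment period is 12 weeks, separate from the run-in week.

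**The concern.** A participant allocated to 3L cannot wear the allocated bandage and the control bandage in the same week. The choice matters for the analysis because Area1 divides Area2 in the primary endpoint. A baseline should not be affected by the treatment under comparison. If the allocated bandage goes on at screening and the Day 1 area is used, it is affected. The endpoint then measures change from a point one week into treatment, and whatever the bandages did differently in that week is lost from the contrast.

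The 12-week clock has the same weakness, since it starts at randomisation in one place and after the run-in week in another. The pilot is also meant to supply the variability of the 12-week reduction for a larger trial, and that variability depends on which area and which interval are used.

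**Working it through.** **The plan's own figure.** Inputs from Sample Size and Analysis plan: mean reductions of 50% and 20%, SD 0.5, two-sided alpha 0.05, power 80%.
- Difference on the log scale: ln(0.8/0.5) = 0.470, as stated.
- n per group = 2 × [0.5 × (1.960 + 0.842) / 0.47]² = 17.77, rounded up to 18, as stated.
- Allowing for 20% loss: 18 / 0.8 = 22.5, rounded up to 23 per arm and 46 in total, as stated.

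The sample size reproduces and does not depend on the run-in question.

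**What each reading does to the endpoint.** Write S for the screening area, D for the Day 1 area and A2 for the area at Table 1's week 12 visit. Then

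log(A2/S) = log(A2/D) + log(D/S).

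The last term is the run-in week. Taking the difference in means between arms:

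| Run-in bandage | Area1 | Consequence |
|---|---|---|
| As allocated | Screening | Area1 precedes treatment; the contrast covers about 13 weeks of allocated treatment |
| As allocated | Day 1 | Area1 is post-randomisation and affected by treatment; the between-arm difference in log(D/S) is removed |
| Standard for all | Screening | log(D/S) has the same expectation in both arms; the expected contrast is unchanged, though its variance may differ |
| Standard for all | Day 1 | Area1 precedes the Day 1 change of bandage; the contrast covers 12 weeks |

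Only the second row biases the denominator. Nothing in the protocol rules it out: the Screening Evaluation text gives the first cell, and Table 1 schedules the Day 1 area. Other baselines do not settle the visit either. The SF 36 and CWIS are placed at the screening visit in their own section, but at Day 1 in Table 1 and in the Day 1 text.

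**Clock.** With randomisation at the screening visit and a one-week run-in, Table 1's week 12 visit falls at about 1 + 12 = 13 weeks after randomisation. Conversely, 12 weeks from a bandage first applied at screening falls at Table 1's week 12 − 1 = 11 visit. The primary outcome wording and the visit schedule therefore differ by a week if randomisation is at screening.

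**The case against.** **The weight of the text favours a common run-in.** Two statements describe standard compression in that week and one phrase says otherwise. The harm also needs two conditions together: the allocated bandage worn in the run-in, and Day 1 used as Area1. Both points are fair, and they are why the consequence is stated as conditional. They do not remove the contradiction.

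**The timing of randomisation may not be contradictory.** Completion of screening can mean completion of the eligibility checks at the screening visit, where Table 1 puts randomisation. This stands, so the point does not rest on it. That reading does, however, place randomisation a week before Day 1, which is the situation in which the run-in bandage matters.

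**Naming the baseline visit can be left to the analysis plan.** This also stands. Silence on the visit would not be a finding alone. It matters here because the contradictory run-in text makes one of the two candidate areas unsafe.

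**Stronger conclusions that a reader might draw are not supported.**
- *Lost power.* Spreading 0.47 evenly over 13 weeks and dropping one gives 0.47 × 12/13 = 0.434 and, with 18 per group, power of Φ(0.434 / (0.5 × √(2/18)) − 1.96) = 74%. But the plan ties 0.47 to a 12-week follow-up, and Day 1 to week 12 still holds 12 weeks of allocated treatment. A larger first-week share would be an assumption without any source in the protocol.
- *A common run-in week dilutes the contrast.* With a screening baseline, the decomposition above shows that the extra week leaves the expected log difference unchanged.
- *Participants lost in the first week fall out of the intention-to-treat analysis.* This follows only if Day 1 is the baseline and the screening area may not be used. The protocol says neither, and it asks those who drop out to return at week 12.

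**Conclusion.** The contradiction about the run-in bandage is explicit and holds for every participant allocated to 3L. It leaves open a reading in which the primary endpoint's denominator is a post-randomisation, treatment-affected area. Under that reading any first-week difference between the bandages is removed from the comparison. The amount cannot be stated, because the protocol gives no time course for healing in either arm. The one-week mismatch in the 12-week clock follows if randomisation is at the screening visit, as Table 1 shows. The sample size of 18 per group is arithmetically sound and is not part of the finding. The trial is a pilot, so the consequence is mainly for what the endpoint and its SD mean when carried into a larger trial. It should be settled promptly, because 25 of 46 participants had been recruited and two further sites approached.

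**What to change.** 1. Reconcile Primary Outcome, Randomisation, Table 1, Screening Evaluation (with the Day 1 text) and Duration of Treatment into one sequence. State once when randomisation occurs and which bandage is worn in the screening week. That clinical choice belongs to the investigators.
2. Define Area1 as the last area recorded before the first allocated bandage is applied, at the same visit in both arms. If the run-in is common, short stretch worn in that week counts as run-in for control participants too.
3. State one start for the 12-week clock, the same in both arms, and check it against Table 1. Counting from a bandage first applied at screening would put the endpoint at the present week 11 visit, so the schedule or the outcome wording would have to change with it.
4. If a common run-in is kept, release the allocation only after the Day 1 area is recorded.
5. For participants already recruited, record which version was followed and apply the same Area1 definition. Record this by site and period: a control participant wears short stretch under either version, so the bandage worn does not show which applied.

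The cost is a protocol clarification, a memo to sites and a check of existing records, plus a schedule change if the clock start requires one. No new measurement of baseline area is needed, because Table 1 already schedules both areas.
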